### Statistical analysis

For continuous variables that are normally distributed, the mean and SD will be presented. For skewed continuous variables, the median and IQR will be presented. Categorical variables will be summarised as frequencies and percentages. The distribution of demographic and clinical variables will be compared between CWH and without HIV using independent sample t*-*tests for means, Wilcoxon rank-sum test for medians and χ^2^ tests for proportions.

Baseline mean TBLH BMC^LBM^ and LS BMAD Z-scores and the prevalence of low TBLH BMC^LBM^ and LS BMAD Z-score will be compared between CWH and without HIV. Among CWH, the association between a priori defined risk factors (ART duration, ART type, proportion of life on treatment, age at ART initiation, CD4 count, viral load, bone age, pubertal stage, nutrition, socioeconomic status and orphanhood) against size-adjusted BMD will be examined using multivariable linear regression (Z-score as a continuous variable) and multivariable logistic regression (as defined by the Z-score cut-off of <−2). Successful antiretroviral therapy will be defined as a viral load of less than 1000 copies/mL. Paired sample t-test or non-parametric Wilcoxon test will be used to assess for differences in TBLH BMC and LS BMAD on children with and without HIV between baseline and follow-up. Multivariable linear regression will be used to analyse the mean percentage change in TBLH BMC^LBM^ (g) and LS BMAD (g/cm^3^) between children with and without HIV. Models will be adjusted for physical activity, calcium and vitamin D intake. Interaction between the effects of pubertal stage (bone age) and HIV on change in TBLH BMC^LBM^ and LS BMAD will be investigated to see if differences in bone density become more or less pronounced through puberty, that is, whether catch-up growth is possible, see figure 2. The regression coefficient (β) for percentage change in size-adjusted bone mass may suggest either no growth impairment (figure 2A), delayed puberty while maintaining the same growth trajectory (figure 2B) or delayed puberty with a reduced growth trajectory (figure 2C) in CWH. If β is markedly more positive in CWH, this suggests that catch-up growth may be possible (figure 2D). Pubertal delay in this study will be defined as the lack of the initial signs of puberty (Tanner stage 2) at an age that is more than 2 SD beyond the population mean^51^ and as chronological age minus bone age >2 years.^52^ Data for total body and lumbar spine DXA, tibial pQCT, hand grip strength and standing long jump in CWH will be analysed with reference to the comparator group of children without HIV.

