Another mechanism by which HIV may exert effects on BMD is through its effect on puberty. Even in the presence of ART, the onset of puberty is delayed by approximately a year in CWH in both high-income^30^ and low-income settings.^31^ Older age at ART initiation has been shown to be a significant risk factor for pubertal delay in Zimbabwean CWH.^31^ Pubertal delay in HIV may be mediated through nutritional deficiency, recurrent infection or chronic immune activation disrupting hormonal regulation.^31^ Delayed puberty may be advantageous for linear growth; spending more time in puberty may allow more time for skeletal growth.^31^ Conversely, delayed puberty has been shown in studies in high-income settings to be detrimental to bone mass accrual.^32 33^ However, the impact of pubertal delay on BMD in low-income countries remains unknown. Pubertal delay can be assessed objectively using hand radiographs. Analysis of the growth plate development and fusion of long bones in the hands can accurately quantify bone age, which is a measure of skeletal maturation. Bone age lagging behind chronological age reflects pubertal delay.^34^

BMD is commonly measured by dual-energy X-ray absorptiometry (DXA) as two-dimensional (areal) BMD; however, this is highly dependent on bone size.^35^ DXA underestimates areal bone density in short children, with smaller bones, and overestimates BMD in taller children, with bigger bones, despite the fact that they may have identical volumetric BMD. Size adjustment of DXA measures is therefore critically important in children with chronic diseases such as HIV, where smaller size due to poorer growth and delayed puberty may explain findings of lower BMD. The two ‘gold standard’ size-adjustment techniques chosen from the International Society for Clinical Densitometry are as follows: bone mineral apparent density at the lumbar spine (LS BMAD) and regression based total-body less-head (TBLH) bone mineral content (BMC) for lean mass adjusted for height (TBLH BMC^LBM^)^36^ Z-scores. As there are currently no published reference DXA data for child or adolescent populations in SSA, in this study we will use the best available data sets from high-income countries such as the UK^36^ to generate Z-scores.

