#### Recruitment of children with HIV

Systematic quota-based sampling by age and sex will be used to recruit 300 children from Parirenyatwa and Harare Hospital HIV clinics. Participants will be recruited sequentially as they attend clinic such that 50 male and 50 female will be chosen for each of three age strata: 8–10.99, 11–13.99 and 14–16.99 years. A maximum of five participants will be enrolled on each day for logistical reasons. The total number of children approached each day will be recorded, irrespective of whether they are subsequently eligible or enrolled to determine the sampling fraction. Written consent will be obtained from children and their guardians. Study processes and procedures will be clearly explained to children and their guardians and they will be given the option to accept or decline to take part in the research. It will also be explained that they are allowed to withdraw from the study at any time, for any reason, without affecting the care they receive from the clinic.

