### Sample size

The sample size was calculated to detect differences in DXA-measured mean size-adjusted bone BMD Z-scores between children with and without HIV. This study will have 80% power (α 0.05) to detect a 0.23 Z-score difference between 300 HIV-infected and 300 uninfected children, assuming an SD of 1.3. As there were no published studies from low income countries, estimates of the expected difference were taken from a US study of children with HIV aged 7–15 years.^10^ In addition, our study will have 80% power to detect a 4.8% difference in the prevalence low size-adjusted BMD between the two groups. This is a smaller prevalence difference than that detected by the most conservative prevalence estimate of low BMD of 7% from three studies in high-income and middle-income countries.^10–12^

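### Three ART-timing variables that determine one another are listed together for the risk-factor models, so their separate coefficients would not be interpretable, and the logistic version has only 1.9 to 8.7 events per listed factor

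*Protocol article*

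**What the plan says.** The Statistical analysis section of the protocol names the risk factors to be related to size-adjusted BMD among children with HIV: "ART duration, ART type, proportion of life on treatment, age at ART initiation, CD4 count, viral load, bone age, pubertal stage, nutrition". Orphanhood and a socioeconomic measure complete the list, which makes eleven in all. Two models are named for them. The first is "multivariable linear regression (Z-score as a continuous variable"). For the binary outcome the plan names "multivariable logistic regression (as defined by the Z-score cut-off of <−2"). The section gives no order of entry, no rule for overlapping variables and no statement of which model is the main one.

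The number of children comes from the recruitment section: "Systematic quota-based sampling by age and sex will be used to recruit 300 children". The Sample size section cites the "most conservative prevalence estimate of low BMD of 7"%, and the Introduction also gives 24% and 32% from other countries.

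On the link between ART timing and puberty, the Introduction states: "Older age at ART initiation has been shown to be a significant risk factor for pubertal delay in Zimbabwean CWH". It adds that studies in high-income settings found delayed puberty harmful to bone accrual.

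**The concern.** Investigating risk factors is a listed aim of the study. The Introduction singles out late ART initiation as a critical reason why bone accrual may be poorer in low-income countries, and the Discussion hopes to find factors that can be acted on. ART timing is therefore an exposure on which readers will want a clear answer.

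The listed model handles that exposure poorly in three ways:

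- Duration, age at initiation and proportion of life on treatment are three descriptions of one history. A coefficient for one with the other two held fixed describes a contrast that no uninterrupted treatment history can show.
- Bone age and pubertal stage sit in the same list, although the protocol itself describes late ART as a cause of pubertal delay.
- The binary outcome may supply few events for eleven factors.

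Because the link between the timing variables is non-linear, software would return estimates, possibly without any warning.

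**Working it through.** **Inputs.** From the protocol: 300 children with HIV, 100 in each of three age strata from 8 to 16.99 years; at least 2 years on ART; eleven listed factors; prevalences of low BMD of 7%, 24% and 32%. Not given: the distribution of age at ART initiation in this cohort, which is assumed below. The protocol states no event count for the risk-factor models, so there is no figure of its own to reproduce.

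**Step 1: the identity.** Write A for age at initiation, D for duration and P for proportion of life on treatment. Without interruption, A + D = current age and P = D / (D + A). Two children with D = 2 illustrate this. Starting at 8 gives P = 2/10 = 0.20; starting at 6 gives P = 2/8 = 0.25. A cannot change with both D and P fixed. This step needs no assumption about distributions.

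**Step 2: size of the overlap.** Simulation: 200 runs of 300 children, age uniform within strata, A capped at current age minus 2 years, bone age = age − 1 + normal error (SD 1.2), and pubertal stage in three levels cut from bone age. Median variance inflation factors (VIF) with D, P, A, bone age and pubertal stage all entered:

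| Assumed age at ART initiation | D | P | A |
|---|---|---|---|
| Uniform, up to 15 years | 15.0 | 26.3 | 20.0 |
| Uniform, up to 8 years | 14.6 | 25.1 | 15.3 |
| Gamma, mean 2 years | 10.1 | 22.6 | 16.5 |
| Gamma, mean 4 years | 15.7 | 24.4 | 16.0 |
| Gamma, mean 6 years | 20.0 | 26.2 | 15.9 |

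Standard errors grow by √VIF, from √10.1 = 3.2-fold to √26.3 = 5.1-fold. With only the three timing variables entered, the VIFs are 3.7–9.5 (D), 22.3–26.1 (P) and 9.1–14.9 (A). Dropping P but keeping bone age and pubertal stage leaves 7.6–12.5 for D and 2.7–9.9 for A, because bone age stands in for age.

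**Step 3: events for the logistic model** (each bone measure separately, before missing data). Events = 300 × prevalence; the last column assumes 14 parameters because some factors have several levels.

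| Prevalence | Events | Per listed factor (÷11) | Per parameter (÷14, assumed) |
|---|---|---|---|
| 7% | 21 | 1.9 | 1.5 |
| 24% | 72 | 6.5 | 5.1 |
| 32% | 96 | 8.7 | 6.9 |

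Ten events per listed factor, a common rule of thumb, would need 110/300 = 37%.

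**Step 4: both together.** Logistic fits were simulated with eleven predictors (500 runs, gamma mean 4 years, no true timing effect, one unrelated factor with true log odds ratio 0.405):

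| Prevalence | SE per SD, P | SE per SD, unrelated factor | 95% CI for P's odds ratio, multiply or divide by | Mean estimate, unrelated factor |
|---|---|---|---|---|
| 7% | 1.23 | 0.25 | 11.2 | 0.440 |
| 24% | 0.72 | 0.15 | 4.1 | 0.436 |
| 32% | 0.66 | 0.14 | 3.6 | 0.427 |

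The ratio of the two standard errors stays near 5 (1.23/0.25 = 4.9; 0.66/0.14 = 4.7), so more events do not cure the overlap. No fit failed.

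**Step 5: the pathway.** The Introduction runs from late ART to delayed puberty, and from delayed puberty to poorer bone accrual. A model holding bone age and pubertal stage fixed estimates only what is left of the timing effect outside that pathway.

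**The case against.** The strongest reply is that the protocol does not say that all eleven factors enter one model. The list could be read as candidate exposures, each examined with some adjustment, and the details may sit in an analysis plan that is not shown. That stands as a limit: joint entry is the natural reading of a list attached to a multivariable model, but it is an inference. It does not remove the point. All three timing variables are named for the same models, and data-driven selection among near-duplicates would itself be unstable.

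A reader might also infer stronger conclusions that the documents do not support:

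- *That the model cannot be fitted.* Exact collinearity arises only if chronological age is added, and age is not listed. The listed variables are related non-linearly.
- *That there are about two events per factor.* This holds only at 7%, a US figure used for the comparison between groups. The Introduction expects risk to differ in low-income countries.
- *That every coefficient is unstable.* The linear model has 300 children and no shortage of events. In the simulated logistic fits the unrelated factor was only slightly biased (0.44 against 0.405 at 7%).

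It is also fair to say that puberty interests the protocol in its own right. A secondary outcome asks how far pubertal delay explains changes in bone and muscle, and an interaction of pubertal stage with HIV is planned. Those analyses concern change by HIV status, not ART timing within children with HIV, so they do not settle the adjustment question here. Finally, the linear model is already planned; what is missing is its priority over the logistic one.

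**Conclusion.** The point holds in a bounded form. On the natural reading of joint entry, the separate coefficients for ART duration, proportion of life on treatment and age at initiation cannot be interpreted as distinct effects, in the linear or the logistic model. Their standard errors are inflated about three- to five-fold when bone age and pubertal stage are also entered. Adjusting for those two also takes out part of the timing effect. The logistic model is thin throughout the cited prevalence range and very thin at its lower end.

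The identity rests only on uninterrupted treatment. The event counts rest on 300 complete records and on prevalences that other studies report for low BMD, which may not match the size-adjusted definition used here. The VIFs and standard errors rest on assumed distributions. The primary outcomes are not affected. The Discussion concedes low power for individual ART types only, so this weakness is not already acknowledged.

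**What to change.** Reword the risk-factor paragraph of the Statistical analysis section as follows:

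1. Enter one ART-timing variable per model, for example age at ART initiation, adjusted for age and sex. Put the other parametrisations in separate, alternative models. With age entered linearly and no interruption, D = age − A, so duration and age at initiation give the same fit with opposite signs. Only proportion of life on treatment is then a different model.
2. Leave bone age and pubertal stage out of the model for the ART-timing effect, add them in a second step, and report both.
3. Name the linear model on the continuous Z-score as the main risk-factor analysis.
4. Limit the logistic model to a few factors named in advance, their number set by the observed event count, or fit it with a penalty such as Firth's.

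The cost is analysis wording only; no data collection changes. Fewer adjusted odds ratios would be reported, and no mutually adjusted timing effects.

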#### Follow-up at 1 year

All study measurements, with the exception of DNA extraction, will be repeated after 1 year. Participants will be recalled exactly 1 year after their first DXA scan. The aim is to perform all scans within a 4-week window period. Contact will be maintained with participants via regular phone calls and text messaging to minimise loss-to-follow-up. The schedule of study procedures is summarised in table 1.

**Table 1 T1:** Summary of study measurements to be quantified at baseline and follow-up

	Measurement	Measurement method	Outcome
Interview-based questionnaire	Sociodemographic characteristics	Questionnaire	Age, sex, school attendance, orphanhood, guardianship
	Clinical history	Questionnaire*	History of fractures and trauma (modified Landin classification^55^) HIV history: age at diagnosis, WHO disease stage, nadir CD4 count, opportunistic infections† ART regimen/duration† Exposures: steroid use, smoking, alcohol, recreational drugs Family history of musculoskeletal disease and fractures Other comorbidities
	Physical activity	The International Physical Activity Questionnaire (IPAQ)^45^ questionnaire (short form)	Median MET-minutes‡ of physical activity/week Inactive (<600 MET-minutes/week) Minimally active (600–1499 MET-minutes/week) Highly active (≥1500 MET-minutes/week)
	Nutrition‡	Dietary assessment tool (Modified Short Food Frequency Questionnaire^46^)	Daily dietary calcium and vitamin D intake Prevalence of vitamin supplementation Sun exposure
	Quality of life and disability	Washington Disability Score^56^	Functioning and disability score
Standardised examination	Musculoskeletal examination	Paediatric Gait, Arms, Legs and Spine (pGALS)^48^ ±regional clinical examination	Joint, spine and gait abnormalities
	Pubertal stage	Tanner’s staging^57 58^	Prepubertal (stage 1) Pubertal (stage 2–3) Postpubertal (stage 4 and 5)
	Anthropometry	Height (standing and sitting) Weight Mid-upper arm circumference (MUAC)§	Standing height-for-age (Z-score)¶^59^ Weight-for-age (Z-score)¶^59^ Body mass index (BMI) (Z-score)¶^59^ MUAC (Z-score)¶^59^
	Muscle strength	Jamar dynamometer standing long jump¶	Hand grip strength (kg, Z-score)¶^60^ Jumping distance (cm, Z-score)**^61^
Radiology	Skeletal maturity	Hand/wrist radiograph	Bone age (years)
	Bone and muscle composition	Dual-energy X-ray absorptiometry (DXA) of total body, lumbar spine and hip††	Size corrected DXA measures of TBLH BMC^LBM^ (g), LS BMAD (g/cm^3^) and Z-scores <−2.¶ Lean mass

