	Bone architecture	Peripheral quantitative computed tomography (pQCT)	Trabecular and cortical vBMD (g/cm^3^), total and cortical CSA (mm²), cortical thickness (mm), periosteal and endosteal circumference (mm), SSI (mm^3^), PMI (mm^4^) and CSMI (mm^4^)
Blood tests	Bone markers and DNA	Blood test (DNA extraction and serum saved)	Future testing e.g. Vitamin D, alkaline phosphotase, C-terminal telopeptide (CTX)‡‡
	HIV markers	Blood test	CD4 count, HIV viral load†

*Details of treatment and comorbidities will be confirmed by patient-held medical records where available.

†Denotes assessments to be carried out in HIV-infected participants only.

‡Energy requirements defined in METS (multiples of the resting metabolic rate that give a score in MET-minutes).

§Nutritional indicator to include composite information from history (usual diet last month, sun exposure–vitamin D status) and clinical examination (MUAC). Similar methods have been used in other low-income contexts.^46^

¶Age-specific and sex-specific Z-scores for (1) anthropometric measures will be determined using the WHO child growth standards.^59^ (2) Hand grip strength will be determined with reference to the uninfected comparison group and European normative data.^60^ (3) Jumping distance will be determined using normative data from South Africa.^61^ (4) Low BMD will be determined with reference to published paediatric Hologic DXA reference databases for LS BMAD and TBLH BMC^LBM^ Z-scores.^36^

**Standing long jump; the longest distance after two attempts will be recorded.

††Pregnancy urine dipstick in female participants prior to DXA if uncertain pregnancy status.

‡‡Tests to be carried out on stored blood when further funding is secured.

CSA, cross-sectional area; CSMI, cross-sectional moment of inertia; DXA, dual-energy X-ray absorptiometry; LS BMAD, lumbar spine bone mineral apparent density; PMI, polar moment of inertia; SSI, Strength Strain Index; TBLH BMC^LBM^, total-body less-head bone mineral content for lean mass adjusted for height.

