### Outcome measures

The primary study outcomes are as follows:

Mean size-adjusted bone density Z-scores; TBLH BMC^LBM^ and LS BMAD.^36^
The prevalence of low TBLH BMC^LBM^ and LS BMAD Z-score<−2 at baseline.^36^

Secondary study outcomes are as follows:

Prevalence of low muscle function; grip strength and standing long jump-for-age (Z-score<−2) and musculoskeletal abnormalities/disabilities by HIV status at baseline.Mean percentage change in TBLH BMC^LBM^ (g) and LS BMAD (g/cm^3^), tibial cortical and trabecular volumetric BMD (g/cm^3^), total cross sectional area, cortical thickness and bone strength, muscle mass and function at baseline and 1 year, by HIV status.Assessment of the extent to which pubertal delay explains changes in these bone and muscle outcomes.

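### The one-year total-body outcome is a percentage change in grams of a measure otherwise used as a size-adjusted Z-score, so the size adjustment behind the catch-up reading is not secured

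*Protocol article*

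**What the plan says.** The Introduction of the protocol article gives the total-body measure as "regression based total-body less-head (TBLH) bone mineral content (BMC) for lean mass adjusted for height (TBLH BMC^LBM^)^36^ Z-scores". It argues that "Size adjustment of DXA measures is therefore critically important in children with chronic diseases such as HIV", because smaller size from poorer growth and later puberty may itself account for low density readings. Under Outcome measures the first primary outcome stays on that scale: "Mean size-adjusted bone density Z-scores; TBLH BMC^LBM^ and LS BMAD".

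The scale changes for the one-year comparison:

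- Table 1, under Follow-up at 1 year, lists "Size corrected DXA measures of TBLH BMC^LBM^ (g), LS BMAD (g/cm^3" (the unit of LS BMAD is cut short here) and then Z-scores.
- The secondary outcome begins "Mean percentage change in TBLH BMC^LBM^ (g) and LS BMAD (g/cm^3".
- The planned regression is of "mean percentage change in TBLH BMC^LBM^ (g) and LS BMAD (g/cm^3^) between children with and without HIV", with physical activity, calcium intake and vitamin D intake as the stated covariates.
- The paired test in the same section concerns "differences in TBLH BMC and LS BMAD on children with and without HIV between baseline and follow-up", without the lean-mass superscript.

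The footnote to Table 1 expands the abbreviation as "TBLH BMC^LBM^, total-body less-head bone mineral content for lean mass adjusted for height" and gives neither a unit nor a derivation. The Statistical analysis section describes the coefficient as one for size-adjusted bone mass. It takes a markedly more positive value in children with HIV as a sign that catch-up is possible (figure 2D).

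**The concern.** The catch-up conclusion depends on the coefficient describing bone relative to body size. For the total-body site, three features of the text leave that unsecured: the gram unit, the plain label in the paired test, and the absence of height and lean mass from the change model.

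The Introduction expects puberty to start about a year late in children with HIV, so the two groups may gain height at different rates during the follow-up year. If the gram quantity still carries body size, that difference goes into the coefficient. The total-body part of the catch-up question could then be answered partly by linear growth. A paired test on unadjusted BMC in growing children would mainly detect growth.

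**Working it through.** The article states no mean, SD or target difference for the one-year outcome. Its sample-size figures concern baseline Z-scores and prevalence, so there is no planned figure to reproduce here. The check is of definitions, followed by an illustration.

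**1. Can the stated quantity be computed on the Z-score scale?** Percentage change is 100 × (z1 − z0) / z0. Take the same gain of 0.2 from four starting points:

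| z0 | z1 | Percentage change |
|---|---|---|
| −2.0 | −1.8 | −10% |
| −0.5 | −0.3 | −40% |
| −0.1 | +0.1 | −200% |
| +0.1 | +0.3 | +200% |

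Identical gains differ in sign and in size by a factor of 20. The outcome therefore cannot be a percentage change of the Z-score, and a gram version is needed.

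**2. Is a gram version defined?** No. Table 1 calls it size corrected and the Statistical analysis section calls its change size-adjusted, but no section says how grams are adjusted. The derivation matters. One possible construction is observed BMC, minus BMC predicted from height and lean mass, plus a constant. If the prediction uses baseline size at both visits, it cancels:

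(BMC1 − pred0 + c) − (BMC0 − pred0 + c) = BMC1 − BMC0

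The gram change is then the raw change, although each value carries the label adjusted. If each visit's own height and lean mass are used, growth in size is taken out. The article does not say which applies.

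**3. Does the model restore the adjustment?** The listed covariates are physical activity, calcium and vitamin D intake. None of them is a measure of body size.

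**4. What could be at stake if the grams are unadjusted?** Assumptions, none from the article: BMC is proportional to height^k with k from 2 to 3, starting height is 130 to 150 cm, one group gains 6 cm and the other 5 cm, and size-adjusted bone does not change in either. The percentage gain is 100 × [((h0 + g) / h0)^k − 1].

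| h0 | k | g = 5 cm | g = 6 cm | Difference in points |
|---|---|---|---|---|
| 130 cm | 2 | 7.8% | 9.4% | 1.60 |
| 130 cm | 3 | 12.0% | 14.5% | 2.51 |
| 150 cm | 2 | 6.8% | 8.2% | 1.38 |
| 150 cm | 3 | 10.3% | 12.5% | 2.15 |

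A 1 cm difference in yearly height gain thus gives a difference of about 1.4 to 2.5 points that says nothing about bone relative to size.

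**The case against.** A reader might infer that the gram quantity simply is raw BMC, and that height gain will therefore be reported as catch-up. The documents do not support that. In the Introduction the abbreviation stands before the word Z-scores, so it can be read as naming the adjusted measure, with the Z-score as a further step. Table 1 lists grams and Z-scores as separate outputs and labels the former size corrected. A regression-adjusted value in grams is possible, and if the adjustment sits in the outcome, leaving height out of the covariates is no defect. The label in the paired test may be a lost superscript, and that test makes no comparison by HIV status. These points stand, and they limit the concern to what can happen.

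Four further points also have force:

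- The catch-up question is examined through an interaction of HIV with pubertal stage (bone age), which compares children of similar maturity and should reduce a bias from different tempo. It is still not an adjustment for height or lean mass.
- Objective 3 asks about accrual of bone mass, of which growth in bone size is a legitimate part. The Statistical analysis section nevertheless claims a size-adjusted reading, and the Discussion rests its catch-up claim on size adjustment.
- A larger shift can be produced by comparing a child who gains 1% in height with one who gains 4%: under the same scaling, 2.0 to 3.0% against 8.2 to 12.5%, or about 6 to 9 points. That contrasts two individual children, has no source in the article, and is not an estimate for group means.
- A condensed article may leave a derivation to the full protocol or analysis plan. That would excuse a missing equation. It does not reconcile the differing scales and labels printed in the article.

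**Conclusion.** The concern holds in a limited form. For the total-body site, the measure used as a size-adjusted Z-score for the primary outcome reappears as a percentage change in grams with no gram version defined. The accompanying paired test names the unadjusted quantity, and the change model has no size term. As written, the size adjustment that the Introduction calls for is not assured where the catch-up conclusion is drawn.

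Whether bias results depends on two things that the article does not settle: whether the grams are unadjusted or only partly adjusted, and whether the groups differ in height gain. The 1.4 to 2.5 points are conditional on the assumed scaling, starting heights and a 1 cm per year difference.

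The reach is one component of a secondary outcome. The baseline primary outcomes, LS BMAD and pQCT volumetric density are untouched. It should still be corrected, because this component supplies the total-body answer on catch-up.

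**What to change.** Make Table 1, Outcome measures and Statistical analysis agree on one of two analyses:

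1. Compare the groups on absolute change in the TBLH BMC^LBM Z-score, with each Z-score computed from height and lean mass measured at that visit. A follow-up analysis adjusted for the baseline Z-score belongs only in a sensitivity analysis. The groups are not randomised and a deficit is expected already at baseline, so conditioning on a baseline measured with error can itself create a group difference.
2. Model TBLH BMC in grams with height and lean mass from both visits in the model.

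Run the paired test on the same size-adjusted Z-score, or delete it. If raw accrual of BMC is also wanted for objective 3, report it separately and do not interpret it as size-adjusted catch-up.

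The cost is rewording. Apart from DNA extraction, all measurements are repeated at one year, so the inputs are already collected at both visits.
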